### **Major vascular complications (at 28 days, 6 months, and 1 year after surgery)**

It is defined as a composite of vascular death, and non-fatal myocardial infarction (or myocardial injury for the 28-day time point), stroke, symptomatic proximal venous thromboembolism, and cardiac arrest. The definitions for the components of the composite are the following:

#### *Myocardial Injury after Noncardiac Surgery (MINS)*

MINS is defined as any myocardial infarction (as defined below), and any elevated troponin (higher than the local lab threshold) judged to be due to myocardial ischemia (i.e. without evidence of a non-ischemic etiology [e.g. chronic elevation, PE, sepsis, cardioversion]) that occurred within the first 28 days after the initiation of surgery. The only exceptions to the definition of an elevated troponin will be to use a higher threshold for TnT of  $\geq 30$  ng/L, and for hsTnT of 20 to  $< 65$  ng/L with an absolute change of at least 5 ng/L or an hsTnT level  $\geq 65$  ng/L. These thresholds for TnT and hsTnT are based upon data from a large international prospective perioperative cohort study that established troponin thresholds that were independently associated with 30-day mortality after noncardiac surgery.

#### *Myocardial Infarction*

If the diagnostic criteria for myocardial infarction includes an elevated troponin, then the definition of MINS must be met to fulfill the diagnostic criteria for myocardial infarction (4th universal definition). The diagnosis of myocardial infarction requires any one of the following criteria.

1. Detection of a rise or fall of a cardiac biomarker (preferably troponin) with at least one value above the 99th percentile of the upper reference limit (URL) together with evidence of myocardial ischemia with at least one of the following:
  - A. ischemic signs or symptoms (i.e., chest, arm, neck, or jaw discomfort; shortness of breath, pulmonary edema);
  - B. development of pathologic Q waves present in any two contiguous leads that are  $\geq 30$  milliseconds;
  - C. new or presumed ECG changes indicative of ischemia (i.e., ST segment elevation  $\geq 2$  mm in leads V1, V2, or V3 OR  $\geq 1$  mm in the other leads], ST segment depression  $\geq 1$  mm], or symmetric inversion of T waves  $\geq 1$  mm) in at least two contiguous leads;
  - D. new left bundle branch block (LBBB); or
  - E. new cardiac wall motion abnormality on echocardiography or new fixed defect on radionuclide imaging
  - F. identification of intracoronary thrombus on angiography or autopsy
2. Cardiac death, with symptoms suggestive of myocardial ischemia and presumed new ischemic ECG changes or new LBBB, but death occurred before cardiac biomarkers were obtained, or before cardiac biomarker values would be increased.
3. PCI related myocardial infarction is defined by elevation of a troponin value ( $>5 \times$  99th percentile URL) in patients with a normal baseline troponin value ( $\leq$ 99th percentile URL) or a rise of a troponin measurement  $>20\%$  if the baseline values are elevated and are stable or falling. In addition, either (i) symptoms suggestive of myocardial ischemia or (ii) new ischemic ECG changes or (iii) angiographic findings consistent with a procedural complication or (iv) imaging demonstration of new loss of viable myocardium or new regional wall motion abnormality are required.
4. Stent thrombosis associated with myocardial infarction when detected by coronary angiography or autopsy in the setting of myocardial ischemia and with a rise and/or fall of cardiac biomarker values with at least one of value above the 99th percentile URL.
5. CABG related myocardial infarction is defined by elevation of cardiac biomarker values ( $>10 \times$  99th percentile URL) in patients with a normal baseline troponin value ( $\leq$ 99th percentile URL). In addition, either (i) new pathological Q waves or new LBBB, or (ii) angiographic documented new graft or new native coronary artery occlusion, or (iii) imaging evidence of new loss of viable myocardium or new regional wall motion abnormality.
6. For patients who are believed to have suffered a myocardial infarction within 28 days of a MINS event or within 28 days of a prior myocardial infarction, the following criterion for myocardial infarction is required:  
 Detection of a rise or fall of a cardiac biomarker (preferably troponin) with at least one value above the 99th percentile of the URL and 20% higher than the last troponin measurement related to the preceding event together with evidence of myocardial ischemia with at least one of the following:
  - A. ischemic signs or symptoms (i.e., chest, arm, neck, or jaw discomfort; shortness of breath, pulmonary edema);
  - B. development of pathologic Q waves present in any two contiguous leads that are  $\geq 30$  milliseconds;
  - C. new or presumed new ECG changes indicative of ischemia (i.e., ST segment elevation  $\geq 2$  mm in leads V1, V2, or V3 OR  $\geq 1$  mm in the other leads], ST segment depression  $\geq 1$  mm], or symmetric inversion of T waves  $\geq 1$  mm) in at least two contiguous leads;
  - D. new LBBB; or
  - E. new cardiac wall motion abnormality on echocardiography or new fixed defect on radionuclide imaging
  - F. identification of intracoronary thrombus on angiography or autopsy

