#### **2.1.2 Secondary objectives**

In patients aged 55 or older, with confirmed or suspected gynecologic cancer, undergoing cytoreductive or high-risk surgery with or without chemotherapy:

1. to compare the predictive performance of *different preoperative/perioperative frailty assessments* for all-cause death or new disability at 6 months after surgery; the different assessments will include:
  - a. different frailty tools, i.e., the whole FP, the single components of the FP, and the CFS;
  - b. a *dynamic* perioperative frailty assessment (i.e., based on a frailty assessment repeated 28 days after surgery, in addition to a preoperative frailty assessment)
  - c. a frailty assessment combining the FP with a cognitive assessment (i.e., *cognitive frailty*)
2. to compare different frailty assessments upon *feasibility* and *acceptance* to patients and healthcare providers;
3. to explore the predictive performance of frailty assessments upon *chemotherapy-related outcomes*, including completion, satisfaction/regret, impact on function, high-grade adverse events and total dose received;
4. to explore the predictive performance of preoperative frailty versus a preoperative cardiovascular risk assessment+age with postoperative trajectories of disability up to 1 year after surgery;
5. to explore the predictive performance of a preoperative frailty assessment and of a preoperative cardiovascular risk assessment based on RCRI+age upon *postoperative outcomes at 28 days after surgery*, including all-cause death or new disability; major vascular events; infection and sepsis; length of stay; unplanned admission to intensive care unit; and delirium.
6. to explore the predictive performance of a perioperative frailty assessment and of a perioperative cardiovascular risk assessment based on RCRI+age combined with MINS, upon other *long-term postoperative outcomes*, including major vascular events at 6 months and 1 year after surgery; infection and sepsis at 6 months and 1 year after surgery; postoperative cognitive dysfunction at 6 months and 1 year after surgery; all-cause death at 6 months and 1 year after surgery; and all-cause death or new disability at 1 year after surgery.
7. to explore the predictive performance of a perioperative frailty assessments and of a perioperative cardiovascular risk assessment based on RCRI+age combined with MINS, upon *oncologic outcomes* of PFS and overall cancer-specific survival (after surgery) up to 1 year after surgery;

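### Read literally, Appendix II bars any troponin-based non-fatal myocardial infarction after day 28 from the 6-month and 1-year vascular composite, and it defines MINS and infarction in terms of each other

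*Protocol*

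**What the plan says.** The composite is headed "Major vascular complications (at 28 days, 6 months, and 1 year after surgery" in Appendix II and is listed at the same three time points in Section 4.2. Its cardiac component is "non-fatal myocardial infarction (or myocardial injury for the 28-day time point". Myocardial injury therefore enters only at 28 days, and infarction is the non-fatal coronary event meant to carry on afterwards. Objective 6 in Section 2.1.2 includes "major vascular events at 6 months and 1 year after surgery" among the outcomes to be explored.

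The Appendix II entry for MINS has two limbs: "MINS is defined as any myocardial infarction (as defined below), and any elevated troponin" judged to be of ischaemic cause. The sentence ends with the limit "that occurred within the first 28 days after the initiation of surgery". Section 3.1.5 gives the predictor version of MINS with the same 28-day limit but without the infarction limb.

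The Appendix II entry for myocardial infarction opens with a condition on troponin-based diagnoses: "then the definition of MINS must be met to fulfill the diagnostic criteria for myocardial infarction". Six criteria follow. The sixth begins "For patients who are believed to have suffered a myocardial infarction within 28 days of a MINS event", and it also covers an infarction within 28 days of an earlier infarction.

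Section 4.4 sends MINS and infarction to an adjudication committee, uses its decisions in all analyses of these events, and says a plan still to be developed will govern the definitions.

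**The concern.** A condition that borrows the whole MINS definition also borrows its time limit. That limit is sensible for a perioperative predictor. It is out of place in an outcome to be counted up to 1 year after surgery. A site or adjudicator who follows the text would have to reject an ordinary troponin-positive infarction in month 4, although the composite is meant to include it.

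Two things are at stake. The infarction component of the later composites would gain no troponin-based non-fatal event after day 28. And because the literal rule differs from what the composite evidently intends, adjudicators could split between the two readings and classify like events differently.

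**Working it through.** The protocol gives no figure to reproduce here; the check is a trace of the definitions.

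**Step 1: which infarction criteria can yield a non-fatal event, and do they need a biomarker?**

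| Criterion (Appendix II) | Biomarker needed? | Can be non-fatal? |
|---|---|---|
| 1. Biomarker change plus evidence of ischaemia | Yes, troponin preferred | Yes |
| 2. Cardiac death before biomarkers are available | No | No |
| 3. Related to percutaneous intervention | Yes, troponin | Yes |
| 4. Stent thrombosis | Yes, cardiac biomarker | Yes |
| 5. Related to bypass surgery | Yes, cardiac biomarker | Yes |
| 6. Soon after MINS or an earlier infarction | Yes, troponin preferred | Yes |

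Every route to a non-fatal infarction needs a biomarker. The only route without one is a death.

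**Step 2: apply the opening condition.** When the biomarker is an elevated troponin, criteria 1, 3, 4, 5 and 6 all require MINS to be met.

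**Step 3: apply the MINS time limit to an event after day 28.** There are two ways to read the MINS sentence.

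- *The 28-day limit governs both limbs.* A late event fails at once.
- *The limit governs only the elevated-troponin limb.* A late event must then enter through the infarction limb. But a troponin-based infarction exists only if MINS is met, and MINS is met only if the infarction exists. The text gives no independent ground for admitting the event.

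One reading excludes the event and the other is circular.

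**Step 4: compare with criterion 6.** Take MINS on day 20 and a suspected infarction 20 days later. The interval is 20 days, within the 28 allowed. The event falls on day 20 + 20 = day 40, past the MINS limit. At the extreme, MINS on day 28 allows an event up to day 28 + 28 = day 56. Criterion 6 thus describes infarctions that the opening condition rejects.

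**Step 5: how much follow-up is touched.** Taking 6 months as 182 days (an assumption) and 1 year as 365:

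- 6 months: (182 − 28) / 182 = 154 / 182 = 85%
- 1 year: (365 − 28) / 365 = 337 / 365 = 92%

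These are shares of calendar time in which the rule bites. They are not shares of infarctions.

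**The case against.** The best reply is that the authors plainly did not mean this. The composite confines myocardial injury to 28 days and keeps infarction at 6 months and 1 year, and criterion 6 looks beyond day 28. The opening condition was probably written to import the higher troponin thresholds and the test of ischaemic cause, not the time window. That is likely right about intent, but no sentence says so.

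The adjudication plan may settle the matter. It might, but it is described as still to be developed and would start from Appendix II. The protocol text needs correcting in any case.

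The circularity matters little within 28 days. This stands: an early troponin-based infarction can meet MINS through the elevated-troponin limb without using the infarction limb.

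Three stronger readings are tempting, and the documents do not support them.

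- *No non-fatal infarction after day 28 can count.* Too broad. The condition applies to an elevated troponin, and criterion 1, for example, reads "Detection of a rise or fall of a cardiac biomarker (preferably troponin". Criteria 4, 5 and 6 also speak of cardiac biomarkers. An infarction diagnosed on another biomarker is not literally caught.
- *85% or 92% of infarctions are lost.* The protocol gives neither a rate nor a timing of infarctions. Scheduled troponin testing ends by day 3 or at discharge (Section 5.1), so later events depend on clinical care and may be few among 280 patients.
- *The cardiovascular comparator is harmed most.* Section 1.2.2 links RCRI to perioperative cardiac complications and MINS to mortality, not to late infarction. On the literal rule, every troponin-based infarction that counts would also be a MINS case, which could favour a comparator that contains MINS. No direction of bias can be claimed.

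**Conclusion.** The inconsistency is real. On the wording, a troponin-based non-fatal infarction after day 28 cannot enter the 6-month or 1-year composite, and the reading that might admit it is circular. The conclusion rests on applying the opening condition and the 28-day limit as written, and on no separate rule overriding them; the adjudication plan is not available to check.

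The reach is limited. One component of one exploratory secondary composite is affected, and the size of the loss in events cannot be derived from the protocol. Vascular death, stroke, proximal venous thromboembolism and cardiac arrest still count after day 28. The primary outcome of death or new disability at 6 months does not use infarction. MINS as a predictor is properly limited to 28 days in Section 3.1.5. A reader should not infer that the primary comparison is compromised.

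**What to change.** Reconcile the Appendix II entries for major vascular complications, MINS and myocardial infarction by stating that:

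1. the 28-day limit does not apply when an infarction after day 28 is classified;
2. the MINS condition in the infarction definition refers only to the troponin-threshold and ischaemic-cause parts of the MINS definition;
3. those thresholds do, or do not, also apply to events after day 28, so that any difference between early and late infarction within the composite is deliberate and visible;
4. the condition does not refer back to the infarction limb of MINS, which removes the circle.

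Simply dropping MINS for later events would not be enough. It would leave the mutual reference in place for early events and would not say which troponin thresholds govern late ones.

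The adjudication plan should carry the same wording. The cost is a text amendment to Appendix II and matching text in that plan. No new data are needed. It is best done before events after day 28 are adjudicated.

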#### *Stroke*

Stroke is defined as a new focal neurological deficit thought to be vascular in origin with signs or symptoms lasting more than 24 hours or leading to death.

#### *Symptomatic Proximal Venous Thromboembolism*

Venous thromboembolism that includes symptomatic PE or symptomatic proximal deep vein thrombosis

#### *Symptomatic Pulmonary Embolism (PE)*

The diagnosis of symptomatic PE requires symptoms (e.g., dyspnea, pleuritic chest pain) or signs (e.g., hypoxia, increased work of breathing) and any one of the following:

1. A high probability ventilation/perfusion lung scan,
2. An intraluminal filling defect of segmental or larger artery on a helical CT scan,
3. An intraluminal filling defect on pulmonary angiography, or
4. A positive diagnostic test for DVT (e.g., positive compression ultrasound) and one of the following:
  - A. non-diagnostic (i.e., low or intermediate probability) ventilation/perfusion lung scan, or
  - B. non-diagnostic (i.e., subsegmental defects or technically inadequate study) helical CT scan

#### *Symptomatic Proximal Deep Venous Thrombosis (DVT)*

The diagnosis of symptomatic proximal DVT requires:

1. symptoms or signs that suggest DVT (e.g., leg pain or swelling),
2. thrombosis involving the popliteal vein or more proximal veins for leg DVT OR axillary or more proximal veins for arm DVTs

Any of the following defines evidence of vein thrombosis:

- A. a persistent intraluminal filling defect on contrast venography (including on computed tomography),
- B. noncompressibility of one or more venous segments on B mode compression ultrasonography, or
- C. A clearly defined intraluminal filling defect on doppler imaging in a vein that cannot have compressibility assessed (e.g., iliac, inferior vena cava, subclavian).

#### *Nonfatal cardiac arrest*

Nonfatal cardiac arrest is defined as successful resuscitation from either documented or presumed ventricular fibrillation, sustained ventricular tachycardia, asystole, or pulseless electrical activity requiring cardiopulmonary resuscitation, pharmacological therapy, or cardiac defibrillation.

#### **Infection, and infection with sepsis (28 days, 6 months, and 1 year)**

Infection is defined as a pathologic process caused by the invasion of normally sterile tissue or fluid or body cavity by pathogenic or potentially pathogenic organisms.

The Third International Consensus Definitions Task Force defines sepsis as a “life-threatening organ dysfunction due to a dysregulated host response to infection.” Based on the Third International Consensus Definitions for Sepsis and Septic Shock (Sepsis-3) criteria, sepsis will require a quick Sequential Organ Failure Assessment (qSOFA) Score  $\geq 2$  points due to infection. The qSOFA includes the following items and scoring system:

1. Altered mental status (1 point)
2. systolic blood pressure of 100 mm Hg or less (1 point), and
3. respiratory rate of 22 breaths/min or more (1 point).

#### **In-hospital delirium (28 days)**

Delirium during the first 3 days after surgery or before discharge from the hospital, based on Confusion Assessment Method (CAM). According to CAM, patients are diagnosed with delirium if they meet the first 2 criteria (acute onset with fluctuating course, AND attention deficit), and at least one of the second 2 criteria (disorganized thinking OR altered level of consciousness). Participants will be screened for postoperative delirium while in hospital, twice daily, during the first 3 days after surgery or until discharge (if before 3 days), by research personnel, using the 3D-CAM, or the CAM-ICU any time the participants are in the PACU or in ICU.

#### **Postoperative cognitive changes (at 6 months and 1 year after surgery)**

We will define this outcome based on a binary and continuous variable.

1. Binary: a decrease of  $\geq 2$  points in the MoCA at 6 months or at 1 year after registration compared with baseline (preoperative)
2. Continuous: change in the MoCA score at 6 months or at 1 year after registration compared with baseline (preoperative)

### **Appendix III – Measuring acceptability of frailty assessment**

Study personnel will invite a convenience sample of 10 consenting physicians involved in the perioperative clinical assessment of the study population (e.g., the Gynecologic Oncology group, the Perioperative Medicine Service, etc.), with no experience with frailty tools, to participate in the administration of the FP and CSF; then the study personnel will administer the acceptability questionnaire to the consenting physicians. Patient's acceptability of frailty assessments will be evaluated administering a questionnaire in a purposeful sample of 30 of the main study participants.

#### **Physicians' acceptability**

A convenience sample of 10 consenting physicians involved in the perioperative clinical assessment of the study population (e.g., the Gynecologic Oncology group, the Perioperative Medicine Service, etc.), with no experience with frailty tools, will be invited to participate in the administration of each frailty instrument (FP and CFS). They will be then administered the following questionnaire by research personnel. The questionnaire is a modified version of the OADRI where only items deemed relevant are retained:

The tool is easy to use  
The tool is useful in my practice.  
The wording of the tool is clear and unambiguous.  
My colleagues support use of the tool.  
Patients benefit from use of the rule.  
Using the tool results in improved use of resources.  
The evidence supporting the rule is flawed.  
I'm already using another tool or similar strategy.  
The tool does not account for an important clinical cue.  
The environment I work in makes it difficult to use the tool.

Physicians are asked to rate each item, for each tool, along a 7-point Likert scale including the following options: strongly agree, moderately disagree, slightly disagree, no opinion/don't know, slightly agree, moderately agree, strongly agree.

#### **Patients' acceptability**

Thirty (30) of the main study participants will be selected according to a purposeful sampling to include patients of different age and different levels of frailty according to the study assessments. At the end of each frailty assessment, they will be asked to complete a questionnaire, which includes 3 closed questions accompanied by 2 open questions:

1. On a scale of 0 to 5, with 0 being not easy at all, and 5 being the easiest, how easy was it to complete the Frailty Phenotype assessment, Clinical Frailty Scale, and Cognitive Frailty questionnaires? You may also answer "no opinion or don't know".
  - a. Can you explain why you find it easy to complete the frailty questionnaire or why you did not find it easy to complete the frailty questionnaire?
2. On a scale of 0 to 5, with 0 being not helpful at all, and 5 being the most helpful, how helpful for understanding your health was it to complete the frailty questionnaire? You may also answer "no opinion or don't know".
  - a. Can you explain why you find it helpful to complete the frailty questionnaire or not helpful to complete the frailty questionnaire?
3. Would you complete the frailty questionnaire again?

